# Synergistic effects of repetitive transcranial magnetic stimulation and a dance movement intervention on mild cognitive impairment: study protocol for a four-arm factorial randomized controlled trial

**DOI:** 10.3389/fphys.2026.1931453

**Published:** 2026-09-09

**Keywords:** dance, mild cognitive impairment, randomized controlled trial, rTMS, study protocol

## Abstract

**Background:**

Mild Cognitive Impairment (MCI) represents a critical transitional stage between normal cognitive aging and dementia, characterized by a high conversion rate to Alzheimer’s disease (AD). Current pharmacological interventions provide limited symptomatic relief and do not alter disease trajectory. Consequently, there is an urgent need for effective, multimodal, non-pharmacological interventions. While repetitive Transcranial Magnetic Stimulation (rTMS) and Dance Movement Intervention (DMI) individually show promise in mitigating cognitive decline, their combined synergistic effects in older adults remain uninvestigated. This protocol outlines a randomized controlled trial to evaluate the clinical efficacy of combining rTMS with a culturally tailored DMI (Chinese square dancing) for older adults with MCI.

**Methods:**

This study is designed as a four-arm, single-blinded, parallel-group randomized controlled trial. We aim to recruit 160 community-dwelling older adults (aged 50–85 years) diagnosed with MCI. Participants will be randomly allocated (1:1:1:1) to one of four groups: Combined Intervention (active rTMS + DMI), rTMS Only (active rTMS + social control), DMI Only (sham rTMS + DMI), or a Control Group (sham rTMS + social control). The 12-week intervention phase utilizes intermittent theta burst stimulation (iTBS) targeted at the left dorsolateral prefrontal cortex (DLPFC) and a structured Chinese square dancing program. Assessments occur at baseline, 12 weeks (post-intervention), and 24 weeks (follow-up). The primary outcome is global cognitive function, measured by the Montreal Cognitive Assessment (MoCA). Secondary outcomes assess memory, executive function, electroencephalography (EEG) biomarkers of neuroplasticity (P300), physical performance, and quality of life.

**Discussion:**

This factorial trial will comprehensively evaluate the individual and interactive effects of neuromodulation and physical-cognitive training. By hypothesizing that rTMS will effectively prime cortical excitability to maximize the benefits of the complex sensorimotor demands of DMI, this study aims to establish a scalable, evidence-based multimodal therapy to delay cognitive decline in aging populations.

## Introduction

1

Mild Cognitive Impairment (MCI) represents a transitional stage between normal aging and dementia, characterized by a decline in cognitive function greater than expected for an individual’s age and education level, but without significant interference with daily activities (Gauthier et al., 2006). The global prevalence of MCI is substantial and increasing, particularly among older adults, with estimates ranging from 10% to 20% in individuals over 65 years of age (Petersen, 2016). A significant concern is the high conversion rate of MCI to Alzheimer’s Disease (AD), with approximately 10–15% of individuals with MCI progressing to AD annually, compared to 1–2% in the general older population (Chen et al., 2022). This progression imposes a substantial global burden, including escalating healthcare costs, caregiver strain, and diminished quality of life for affected individuals and their families (Wimo et al., 2017). Effective interventions to prevent or delay conversion from MCI to AD are therefore a public health priority, making MCI a critical target for early intervention.

Despite extensive therapeutic strategies, current interventions for MCI have shown limited efficacy in altering disease progression or providing sustained cognitive benefits. Pharmacological treatments—primarily acetylcholinesterase inhibitors and NMDA receptor antagonists—offer modest symptomatic relief but do not halt neurodegeneration (Kavirajan and Schneider, 2007) and are often limited by side effects and poor adherence. Non-pharmacological approaches, including cognitive training, physical exercise, and dietary interventions, have demonstrated some promise in improving cognitive function and delaying decline (Livingston et al., 2020); however, their effects are often modest, and challenges remain regarding long-term adherence, scalability, and the precise mechanisms underlying their benefits. The heterogeneous nature of MCI also suggests that a single intervention may not be sufficient to address the multifaceted pathology and diverse clinical presentations. Consequently, there is a critical need for novel multi-modal interventions that can synergistically target the complex neurobiological and behavioral aspects of MCI.

Repetitive Transcranial Magnetic Stimulation (rTMS) has emerged as a non-invasive brain stimulation technique with significant therapeutic potential for neurological and psychiatric disorders, including MCI. rTMS operates by generating a rapidly varying magnetic field over the scalp, inducing a transitory electric current in the cortical surface. This current modulates neuronal activity directly beneath the coil and in connected brain regions, enhancing cortical excitability and promoting long-term potentiation (LTP)-like plasticity (Esposito et al., 2022). Specifically, facilitatory protocols such as intermittent theta burst stimulation (iTBS) deliver bursts of high-frequency stimulation (50 Hz) repeated at a theta rhythm (5 Hz), mimicking endogenous learning rhythms in the brain (Sharbafshaaer et al., 2024).

Previous studies have demonstrated that rTMS, particularly when applied to the dorsolateral prefrontal cortex (DLPFC), a region critical for executive function and memory, can improve cognitive performance in individuals with MCI (Guo et al., 2025; Yuan et al., 2025). Recent comparative trials indicate that iTBS over the left DLPFC yields cognitive benefits equivalent to conventional high-frequency rTMS in MCI, while requiring only a fraction of the session time (e.g., 3 vs. 37.5 minutes) (Zheng et al., 2024). rTMS can also modulate functional connectivity within key brain networks, such as the default mode network (DMN) and fronto-parietal network, which are often disrupted in MCI (Esposito et al., 2022; Guo et al., 2025). By directly influencing neural circuits and promoting synaptic plasticity, rTMS may prime the brain to be more receptive to subsequent cognitive and behavioral interventions in MCI. Among various forms of physical activity, dance stands out as a particularly rich, multi-faceted intervention for older adults with MCI. Dance—particularly structured forms such as Chinese square dancing—integrates physical, cognitive, social, and emotional components, offering benefits beyond conventional aerobic exercise (Colcombe and Kramer, 2003; Tao et al., 2023; Wu et al., 2022). It improves cardiovascular fitness, balance, gait speed, and motor coordination, all vital for maintaining physical independence and reducing fall risk in MCI (Sánchez-Alcalá et al., 2025). Learning and executing complex dance sequences demand continuous attention, working memory, planning, and decision-making, providing intensive cognitive training, while synchronizing movements to music and partners further challenges dual-tasking abilities and cognitive flexibility (Quan et al., 2025). Group dance activities foster social engagement and a sense of community—reducing loneliness and isolation, which are known risk factors for cognitive decline and depression in MCI (Cacioppo and Cacioppo, 2018)—while the accompanying music, rhythmic movements, and expressive elements can enhance mood, reduce stress, and provide multisensory input that supports brain health and emotional regulation (Hewston et al., 2021). Chinese square dancing, with its energetic rhythms and group format, is particularly well-suited to delivering these benefits, as it is easy to learn, affordable, and highly popular among older adults in China (Ou et al., 2022).

While both rTMS and dance interventions individually show promise in ameliorating cognitive decline in MCI, their combination is hypothesized to yield synergistic effects that surpass the benefits of either intervention alone. The rationale is grounded in the distinct yet complementary neurobiological and behavioral mechanisms of each modality. Critically, rTMS and dance converge on a shared set of physiological mechanisms—BDNF signaling, cortical excitability, motor-cognitive integration, and neuroplasticity—providing a unifying biological substrate for their synergy. rTMS can induce a state of enhanced cortical excitability and synaptic plasticity, particularly in the DLPFC and its interconnected networks, such as the hippocampus (Esposito et al., 2022; Phipps et al., 2021). This neuromodulatory effect can be conceptualized as ‘priming’ the brain, making it more receptive to the plastic changes induced by subsequent cognitive and physical training (Guo et al., 2025). Dance, with its rich sensorimotor and cognitive demands, can then capitalize on this primed state. Physical activity, including dance, is known to promote the release of neurotrophic factors such as Brain-Derived Neurotrophic Factor (BDNF) and Insulin-like Growth Factor 1 (IGF-1), enhance cerebral blood flow, and stimulate neurogenesis (Ren et al., 2025; J. Zhang et al., 2025). These activity-dependent neurobiological changes can consolidate and extend the neuroplastic effects initiated by rTMS, leading to more robust and sustained cognitive benefits in MCI (Yuan et al., 2025).

The cognitive demands inherent in learning and performing dance routines, such as memorizing steps, coordinating movements, and adapting to music, provide an ideal environment for cognitive rehabilitation. Combined with the targeted neural modulation from rTMS, which can enhance neural efficiency and connectivity in critical cognitive regions, this may yield more profound and lasting improvements in specific cognitive domains (e.g., executive function, memory, attention) and overall global cognition in MCI patients (Quan et al., 2025; Yuan et al., 2025). The engaging and enjoyable nature of dance may further improve adherence to rTMS sessions, maximizing the therapeutic benefits of both interventions. The combined intervention offers a comprehensive approach by simultaneously targeting the neurological underpinnings of MCI through rTMS and addressing the physical, cognitive, social, and emotional dimensions through dance—a multi-modal framework essential for managing a condition as complex as MCI, which affects multiple aspects of an individual’s well-being.

Despite the compelling theoretical rationale for combining rTMS and dance, randomized controlled trials investigating their synergistic effects in older adults with MCI remain scarce. Existing research has largely focused on the individual effects of rTMS or various forms of exercise, including dance, but rarely on their combined impact using a robust factorial design. To our knowledge, no randomized controlled double-blind study has compared rTMS combined with Chinese square dance against appropriate controls, nor comprehensively disentangled the individual contributions of each modality. Therefore, the primary aim of this study is to evaluate the clinical efficacy of combined rTMS and Chinese square dance on cognitive function, neuroplasticity, and physical performance in older adults with MCI. Secondary aims include evaluating the individual effects of rTMS and Chinese square dance and elucidating the potential synergistic mechanisms underlying the combined intervention, thereby providing a robust rationale for future therapeutic strategies in MCI. **Figure 1** illustrates the proposed biological framework of this combined intervention, summarizing the four shared neurobiological pathways—BDNF signaling, cortical excitability, motor-cognitive integration, and neuroplasticity—on which rTMS and DMI are hypothesized to converge to enhance cognitive outcomes in MCI.

**Figure 1 f1:**
[figure not shown]
Proposed synergistic mechanisms of rTMS and DMI in MCI. The figure illustrates the biological rationale underlying the combination of repetitive transcranial magnetic stimulation (rTMS) and Dance Movement Intervention (DMI) in older adults with mild cognitive impairment (MCI). Left panel: rTMS is delivered as intermittent theta-burst stimulation (iTBS) over the left dorsolateral prefrontal cortex (L-DLPFC), which modulates cortical excitability, fronto-parietal network activity, and long-term potentiation (LTP)–like plasticity. Middle panel: DMI integrates motor components (coordination, balance, and cardiovascular fitness) with cognitive components (attention, working memory, motor planning, and executive function). Right panel: Both interventions converge on four shared neurobiological pathways—brain-derived neurotrophic factor (BDNF) signaling, cortical excitability, motor-cognitive integration, and neuroplasticity—which together are hypothesized to yield greater cognitive improvement in MCI than either modality alone.

## Methods and analysis

2

### Trial design

2.1

This study will adopt a four-arm, single-blinded, parallel-group randomized controlled trial (RCT) design, chosen to comprehensively evaluate the individual and synergistic effects of repetitive transcranial magnetic stimulation (rTMS) and a dance movement intervention (DMI). Participants will be randomly assigned in a 1:1:1:1 ratio to one of four parallel groups: (1) a Combined Intervention Group, receiving active rTMS followed by the DMI (Chinese Square Dance); (2) an rTMS Only Group, receiving active rTMS and a time-matched, non-aerobic social activity control; (3) a DMI Only Group, receiving sham rTMS followed by the DMI; and (4) a Control Group, receiving sham rTMS and the social activity control. The research protocol will adhere to the Standard Protocol Items: Recommendations for Interventional Trials (SPIRIT) guidelines (Chan et al., 2013) and the Consolidated Standards of Reporting Trials (CONSORT) statement for non-pharmacologic treatments (Barbour et al., 2017), and the study will be conducted in accordance with the Declaration of Helsinki (Association, 2025) and has been registered at Chinese Clinical Trial Registry (ChiCTR2600127655). All procedures will be carried out at the Department of Rehabilitation, Handan Central Hospital, Handan, China (see **Figure 2**).

**Figure 2 f2:**
[figure not shown]
CONSORT flow diagram illustrating the participant screening, randomization, and allocation process for the four-arm factorial randomized controlled trial. Potentially eligible participants are screened for eligibility and, following exclusion of ineligible individuals, 160 participants are randomized (1:1:1:1) into four parallel groups: Group 1, Combined Intervention (active rTMS + DMI, n = 40); Group 2, rTMS Only (active rTMS + social control, n = 40); Group 3, DMI Only (sham rTMS + DMI, n = 40); and Group 4, Control (sham rTMS + social control, n = 40). Each group undergoes a 12-week intervention phase, a post-intervention assessment at Week 12, a 12-week follow-up phase, and a final assessment at Week 24. rTMS, repetitive transcranial magnetic stimulation; DMI, dance movement intervention.

### Participants

2.2

Participants will be recruited from the Department of Rehabilitation at Handan Central Hospital. A convenience sampling method will be employed, with local physicians providing a list of potentially eligible patients diagnosed with MCI. All participants will provide written informed consent before enrollment. A family member or legal guardian will also be asked to co-sign the consent form. Participant data will be anonymized to ensure confidentiality. The data will be secured during the study and destroyed five years after the study completion.

Inclusion criteria: (1) Diagnosis of amnestic or multi-domain MCI by a specialist physician according to the National Institute on Aging-Alzheimer’s Association (NIA-AA) criteria. (2) Age between 50 and 85 years. (3) Montreal Cognitive Assessment (MoCA) score between 18 and 25. (4) Geriatric Depression Scale (GDS-15) score < 5. (5) Physically able to participate in dance activities without assistive devices and deemed at low risk for falls (Berg Balance Scale score ≥ 41). (6) Stable doses of any prescribed medications for at least 30 days prior to screening. (7) Sufficient visual and auditory acuity (with correction if necessary) to complete assessments and interventions. (8) Voluntarily agrees to participate and provides informed consent.

Exclusion criteria: (1) Diagnosis of dementia (any type). (2) Presence of major psychiatric conditions (e.g., major depressive disorder, schizophrenia) or neurological disorders (e.g., Parkinson’s disease, stroke) that could confound cognitive assessment. (3) Contraindications to rTMS (e.g., history of seizures, metallic implants in the head). (4) Regular participation in structured exercise (≥ 3 times per week) or another cognitive intervention program within the past six months. (5) Abuse of drugs or alcohol that could cause cognitive impairment.

The study would cease if any of the following occurs: (1) Participant’s death. (2) Medical problems related to exercises (fracture, cardiac or cardiopulmonary problems, etc.). (3) Participants experience adverse event(s) that require discontinuation in the judgment of the principal investigator or trial instructor. (4) Participants have a need for additional intervention (such as cognitive treatment) that would interfere with the trial. (5) Participant neglects to follow trial instructions. (6) Participant have lost more than six sessions and cannot make additional lessons to cover the deficiency. (7) Participants or their legally authorized representative request consent withdrawal. An adverse event will be defined as any untoward medical occurrence in a participant during participation in the study. Adverse events include unbearable discomfort with rTMS intervention, falling, tripping, serious muscle soreness during dance participation. Participants will be allowed to finish all dance classes in a sitting position to prevent further adverse events if necessary.

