### Measurement outcomes

2.4

Assessments will be conducted at three time points: Baseline (T0), Post-Intervention (T1, Week 12), and Follow-up (T2, Week 24). T1 assessments will be conducted 24–72 hours after the final intervention session of Week 12, to avoid the potential confounding influence of acute rTMS and dance exposure on cognitive and physical performance. To control for circadian variation, T1 and T2 assessments for each participant will be scheduled at the same time of day as that participant’s T0 assessment. Participants’ self-rated scales will be completed under guidance. All the tests will be administered in accordance with the standard procedures. The specific schedule of enrolment, interventions, and assessments is detailed in **Table 1**.

**Table 1 T1:** SPIRIT schedule of enrolment, interventions, and assessments.

Procedure	*Enrolment*	*Allocation*	*Intervention Phase*	*Post-Intervention*	*Follow-up*
*Timepoint*	-t_1_ (Screening)	T0 (Baseline)	Weeks 1–12	T1 (Week 12)	T2 (Week 24)
Enrolment:					
*Eligibility Screening*	**X**				
*Informed Consent*	**X**				
*Demographics & Medical History*	**X**				
*Inclusion MoCA, GDS-15, BBS*	**X**				
*Randomization*		**X**			
Interventions:					
*Active or Sham iTBS (rTMS)*			**X**		
*Chinese Square Dancing (DMI)*			**X**		
*Social Activity Control*			**X**		
Assessments:					
Primary outcome					
*Montreal Cognitive Assessment (MoCA)*		**X**		**X**	**X**
Secondary outcomes					
*Wechsler Memory Scale (WMS-IV)*		**X**		**X**	**X**
*Trail Making Test (Part A & B)*		**X**		**X**	**X**
*Berg Balance Scale (BBS)*		**X**		**X**	**X**
*6-Minute Walk Test (6MWT)*		**X**		**X**	**X**
*12-item Short Form Survey (SF-12)*		**X**		**X**	**X**
Neurophysiological & exploratory					
*EEG/ERP (P300 Oddball paradigm)*		**X**		**X**	
*Resting-State fMRI (rs-fMRI)*		**X**		**X**	
Safety & fidelity					
*Adverse Events Monitoring*			**X**	**X**	
*Blinding Integrity Questionnaire*				**X**	
*Qualitative Interviews*					**X**

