#### Participants and sampling

2.5.1

A purposive sample of approximately 20–25 participants (5–7 from each intervention group, including the control group) will be recruited for individual semi-structured interviews. This sampling strategy will ensure representation across intervention arms and varying levels of engagement and outcomes. Additionally, 5–7 medical staff (e.g., neurologists, nurses, rTMS technicians, dance instructors) involved in the study will be interviewed to gather perspectives on implementation feasibility, challenges, and perceived benefits.

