#### Data collection

2.5.2

Individual semi-structured interviews will be conducted by a trained qualitative researcher (not involved in direct participant care or intervention delivery) at the end of the 12-week follow-up period (Week 24). Each interview is expected to last approximately 45–60 minutes. Interviews will be audio-recorded with explicit consent and transcribed verbatim. The interview guides will be developed based on relevant literature and the study objectives. For Participants: Acceptability of the intervention (e.g., comfort, enjoyment, perceived burden), satisfaction with the program, perceived cognitive and physical changes, social engagement, and suggestions for improvement. For Medical Staff: Feasibility of implementing the rTMS and dance interventions (e.g., logistical challenges, resource requirements, training needs), perceived participant engagement and response, and overall impressions of the program’s integration into clinical practice.

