#### Quantitative statistics

2.9.1

All quantitative data analyses will be performed using standard statistical software (R, version 4.2). To ensure methodological rigor, the primary efficacy analysis will be conducted in accordance with the intention-to-treat (ITT) principle, encompassing all randomized participants regardless of adherence to the intervention protocols or study completion. A per-protocol (PP) analysis, restricted to participants who complete a pre-defined minimum number of intervention sessions, will additionally be performed as a sensitivity check to assess the robustness of the findings.

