##### Analysis of primary and secondary outcomes

2.9.1.2

To evaluate the individual and synergistic effects of the interventions across the three assessment time points (baseline, Week 12, and Week 24), linear mixed-effects models (LMMs) will be employed. LMMs are particularly well-suited to this trial design, as they accommodate repeated measures, account for intra-subject correlation, and appropriately handle missing data under the missing-at-random (MAR) assumption without necessitating listwise deletion. The outcome measures—including global cognitive function (MoCA), memory, executive function, EEG/ERP parameters, and physical performance metrics—will be modelled as dependent variables. Fixed effects will comprise Group (Combined Intervention, rTMS Only, DMI Only, Control), Time (T0, T1, T2), and the Group × Time interaction term, with the latter serving as the primary indicator of intervention efficacy over the study period. Participant identification will be specified as a random intercept to account for between-subject variability.

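### The cessation list ends participation for non-adherence and, applied as written, loses the Week 12 and Week 24 outcomes that the intention-to-treat analysis needs

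*Protocol article*

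**What the plan says.** Section 2.2 (Participants) gives seven criteria under one consequence: "The study would cease if any of the following occurs". They cover death, exercise-related medical problems, adverse events requiring discontinuation, need for another intervention, two forms of non-adherence, and withdrawal of consent. Criteria (5) and (6), the non-adherence pair, read "Participant neglects to follow trial instructions. (6) Participant have lost more than six sessions and cannot make additional lessons to cover the deficiency". Nothing in the list says whether sessions, assessments or both come to an end.

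Section 2.9.1 defines the primary analysis as intention to treat, "encompassing all randomized participants regardless of adherence to the intervention protocols or study completion". It adds a per-protocol analysis "restricted to participants who complete a pre-defined minimum number of intervention sessions" as a sensitivity check. Section 2.9.1.2 relies on linear mixed models that are said to "appropriately handle missing data under the missing-at-random (MAR) assumption". Section 2.9.1.5 adds multiple imputation as a supplement if more than 10% of data are missing.

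Section 2.4 places T1 24–72 "hours after the final intervention session of Week 12". Table 1 schedules the outcome MoCA at T0, T1 and T2 only.

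**The concern.** An intention-to-treat analysis needs outcomes from people who did not adhere. A rule that ends participation because of non-adherence removes those outcomes by design. The analysis can still count these people as randomised, but it would hold only a baseline score for them and would have to predict their Week 12 result from those who stayed.

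Two things are at stake. First, the primary estimate would drift towards an effect in good attenders, although the protocol promises one in everybody randomised. Second, the per-protocol check would lose much of its value as a contrast, because most of its restriction would already have been applied to the observed data. No analysis plan can repair this afterwards, since an assessment that was never made cannot be recovered.

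**Working it through.** **Inputs**
- Classes: 3 per week for 12 weeks, for dance (section 2.3.2) and for the social control (section 2.3.3).
- rTMS sessions, active or sham: 5 per week for 4 weeks, then 2 per week for 8 weeks (section 2.3.1).
- Removal threshold: more than six sessions lost and not made up (section 2.2, criterion 6).
- MoCA after baseline: T1 and T2 (Table 1).

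**Step 1: how much non-adherence triggers criterion (6).** The criterion speaks of lessons to make up the loss, so it is read here as referring to classes.
- Classes per arm: 3 × 12 = 36.
- More than six means at least 7: 7/36 = 19.4%.
- Attendance at the trigger: 36 − 7 = 29, and 29/36 = 80.6%.
- Lowest attendance among those not removed: 36 − 6 = 30, and 30/36 = 83.3%, counting made-up classes as attended.
- Earliest possible trigger: the seventh class at 3 per week falls in week 3, because 7/3 = 2.33 rounds up to 3.

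If rTMS sessions count as well, the total is 36 + (5 × 4 + 2 × 8) = 36 + 36 = 72, and the trigger is 7/72 = 9.7%. The class-only reading is therefore the more lenient one. Under either reading a retained participant has at most six unrecovered misses, so at least 30 of 36 classes.

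**Step 2: what is observed for a removed participant.** T1 follows the last session, so a seventh unrecovered miss comes before T1. With MoCA scheduled only at T1 and T2 after baseline, 0 of 2 post-baseline scores remain. The primary outcome, the change from T0 to T1, is unobserved.

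**Step 3: what the planned models can do about it.** The covariates in section 2.9.1.4 are age, gender, education and baseline MoCA; attendance is not among them. A participant with only a T0 score adds no information on change, and the missing change is in effect filled in from those in the same arm who stayed. That is valid only if, given these variables, people who miss classes would have changed as attenders did. Section 2.9.3 itself contemplates low adherence or high attrition in the combined arm because of the burden of two modalities, so the loss could differ by arm. The imputation in section 2.9.1.5 specifies no departure from missing at random.

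**Step 4: intention to treat beside per protocol.** If everyone with a T1 score has at least 30 of 36 classes, a per-protocol minimum can change the observed set through class attendance only if it is set above 30 classes.

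**Step 5: sample size.** Section 2.7 needs 128 evaluable participants and allows 20% attrition: 128/(1 − 0.20) = 160, as stated. There is no reserve beyond that allowance, and the causes of attrition named there do not include removal for non-adherence. Whether such removals fall inside the 20% is not said. Keeping stopped participants in follow-up changes none of these figures.

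**The case against.** The strongest reply is that the heading is loose English. Taken literally, one death would end the trial, which nobody intends. The list never mentions assessments. Criterion (3) speaks of discontinuation, criterion (6) of lessons, and the paragraph closes on finishing classes seated, so it may mean only that the intervention stops.

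Other sections point towards retention. Figure 2 and Table 1 schedule T1 and T2 by group with no adherence condition. The Week 24 interviews are to cover "varying levels of engagement and outcomes". Section 2.9.3 treats low adherence and attrition as separate things. Section 2.3.2 logs attendance to support per-protocol analyses, which would have little to do if poor attenders had already gone. The full protocol may also settle the matter, and the 20% allowance may absorb some of the loss.

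Much of this stands as evidence of intent. It does not settle the rule. Section 2.3 describes the study as made up of the intervention phase and the follow-up phase, so its ceasing most naturally ends both, and criteria (5) and (6) share their consequence with death and consent withdrawal. No section says that a stopped participant is still assessed. The point is therefore a stated rule that collides with the stated analysis, and more than a missing detail. An attrition allowance protects numbers but does not deal with selective loss.

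Two qualifications stand. Criterion (6) also requires that the classes cannot be made up, so a trigger in week 3 is possible but many cases would become clear only later. And the per-protocol minimum may also count rTMS sessions, so under the class-only reading the two analyses could still differ in that respect.

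**Conclusion.** The concern holds and should be fixed, with medium confidence because it depends on how the list is applied. Applied as written, section 2.2 removes both post-baseline MoCA scores from anyone with seven or more unrecovered missed classes (19% of 36), and it confines the observed T1 data to people with at least 83% class attendance. That conflicts with the population promised in section 2.9.1. Criterion (5) adds to the problem because it has no threshold.

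The conclusion assumes that cessation covers assessments as well as sessions, and the counts in the form given assume that lost sessions means classes. The documents contain no removal rate and no outcomes for removed participants, so no figure for bias, and no direction, can be given.

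**What to change.** Reword the list in section 2.2 so that criteria (2) to (6) stop or modify the intervention sessions only. Add one sentence: T1 and T2 assessments are sought for every randomised participant except after death or withdrawal of consent to follow-up. Use the session threshold only to define the per-protocol set. Align the consent wording, so that a participant can stop the sessions and still agree to be assessed. When treatment itself should stop remains a decision for the clinical team.

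The cost is a few sentences in the protocol and consent form, plus some effort to bring stopped participants to visits that are already scheduled. The sample size stays at 160. The change is needed before participants are stopped under the present wording, because their outcomes cannot be collected afterwards.
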